## 192 6 STATISTICAL PRINCIPLES

193

### 194 6.1 CONFIDENCE INTERVALS AND *P* VALUES

195

196 Significance was set at  $P < 0.05$ . Results will be expressed with 95% confidence intervals.

## 6.2 ADHERENCE AND PROTOCOL DEVIATIONS

Adherence to the protocol will be defined as attendance at scheduled visits. Adherence to changing dietary patterns and lifestyle will be measured through different surveys and questionnaires. The number (and percentage) of patients with protocol deviations will be summarized for each arm. Results will be provided for each arm. Percentage compliance will be provided for each arm.

## 6.3 ANALYSIS POPULATIONS

Both intention-to-treat and per protocol analyses will be performed.

# 7 TRIAL POPULATION

---

## 7.1 SCREENING DATA

N/A

## 7.2 ELIGIBILITY

The trial inclusion and exclusion criteria are specified in [Table 3](#).

The inclusion criteria to be met by the index subject (male or female) of each family will be: age 18-85 years, and to be part of a family (living together) of at least two members. The other members of the family (either sex) had to be aged 3–85 years.

The following will be deemed reasons for excluding an index subject: alcoholism, undergoing lipid-lowering treatment, pregnancy, cardiovascular disease (ischaemic heart disease, heart failure, peripheral vascular disease, cerebrovascular disease), dementia, or having a predicted survival of less than one year. The exclusion criteria for the family members of the index subject will be the same, except that those following lipid-lowering treatment were included. Finally, for a family to be incorporated into the study, at least two members will meet all inclusion criteria but no exclusion criterion.

225

226 **Table 3.** Inclusion and exclusion criteria.

|                                     | Inclusion criteria                                                                                    | Exclusion criteria                                                                                                                                                                                                                   |
|-------------------------------------|-------------------------------------------------------------------------------------------------------|--------------------------------------------------------------------------------------------------------------------------------------------------------------------------------------------------------------------------------------|
| Individual level             |                                                                                                       |                                                                                                                                                                                                                                      |
| Index subject of each family | Male or female
Age 18-85 years
To be part of a family (living together) of at least two members | Alcoholism
Pregnancy
Cardiovascular disease (ischaemic heart disease, heart failure, peripheral vascular disease, cerebrovascular disease)
Dementia
Predicted survival of less than one year
Lipid-lowering treatment |
| Other family members         | Male or female
Age 3-85 years                                                                      | Alcoholism
Pregnancy
Cardiovascular disease (ischaemic heart disease, heart failure, peripheral vascular disease, cerebrovascular disease)
Dementia
Predicted survival of less than one year                             |
| Cluster (family) level       |                                                                                                       |                                                                                                                                                                                                                                      |
|                                     | Two or more members had to meet all inclusion criteria but no exclusion criterion.                    |                                                                                                                                                                                                                                      |

227 **7.3 RECRUITMENT**

228

229 Families will be chosen via the random selection of index subjects from the National Health  
 230 System records. At this time, a random selection of 3500 individuals aged 18–85 years was  
 231 made, stratified by decade. The chosen subjects will be phone in order to confirm their  
 232 participation in the study. This will provide a list of subjects to whose homes letters  
 233 explaining the project, and an invitation to take part, will be sent. These subjects will be  
 234 again called by telephone to reconfirm their participation, to verify that those interested  
 235 met the inclusion criteria, and to record the size of their families. Those who accept the  
 236 invitation to join the study will be given a pre-assessment appointment at which time the  
 237 project and its aims will be verbally explained, an explanation provided on how subjects  
 238 were selected, what participation would entail, and the rights of subjects made clear.  
 239 Documentation providing the details of the project, and consent forms for the whole family,  
 240 will be also distributed. Those who finally would decide to take part will be invited to return  
 241 to the health centre, accompanied by their families, for baseline monitoring. The  
 242 recruitment rate planned will be 10–15 families per week.

To encourage the population to take part, the study will be advertised in the press, on radio and television, and via posters hung in the health center and the A Estrada City Hall. The family doctors involved will help by answering questions about the project.

A CONSORT flow diagram will be prepared, showing the number of people/families screened, those who were eligible, those who take part, who were randomized, who received the allocated treatment, and who withdrew or were lost to follow-up.

#### 7.4 WITHDRAWAL/LOSS TO FOLLOW-UP

The inclusion of families in the trial naturally ends at 6 months. The directed withdrawal criteria will be the same as the exclusion criteria mentioned above. Not attending programmed appointments and voluntary withdrawal will be also contemplated as withdrawals. Those who will be lost to the study will be not replaced. All reasons for withdrawal/loss will be recorded. This information will be available in the above-mentioned CONSORT diagram.

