### 5.5 SAMPLE SIZE AND POWER ESTIMATE

The sample size needed to ensure adequate statistical power was determined taking into account the mean cholesterol concentration of the study population (200 mg/dl; inter-person standard deviation 36 mg/dl) and assuming that the dietary intervention would be associated with a reduction of 10 mg/dl. Further assumptions included an intraclass correlation coefficient of 0.25, a family size of 2-4 members, a 90% retention rate, and a 0.05 Type I error rate. Sample size and power estimates were calculated using the Sample Size Shop's GLIMMPSE 2.0 online tool for clustered data. It was determined that a sample size of 250 families would provide a statistical power in excess of 80% for detecting differences between the trial arms.

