## 8.3 MISSING DATA

Missing data will be identified and the reason for their absence investigated. When no reason was determined, these data will be deemed missing at random.

The imputation model will include all the variables, including the dependent variables as well as any other variable that might provide information on the probability of missing data, or about the true values for missing data.

To treat the original data and the multiple imputation data, workflows recommended by StataCorps will be followed.

Multiple imputations will be used to account for subjects with baseline results but missing results at the end of the trial, as well for subjects for whom some data could be not available (biomarkers, anthropometric measurements, surveys, questionnaires, etc.).

Fifty imputations will be performed and the results combined using Rubin's Rules. Imputation will be performed separately for the intervention and control arms.

The distribution of imputed variables will be compared to that of the observed and the complete (i.e., observed and imputed) data.

A sensitivity analysis will be performed to assess the robustness of the results obtained. This involved re-analyzing the primary outcome using techniques not based on multiple imputation (available cases).

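### Section 7.4 turns missed appointments and exclusion criteria that arise after randomisation into withdrawals, with no provision for collecting 6-month outcomes afterwards, which weakens the intention-to-treat analysis

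*Protocol*

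**What the plan says.** Protocol section 7.4 gives three routes out of the trial. The first is directed withdrawal: "The directed withdrawal criteria will be the same as the exclusion criteria mentioned above". The others follow: "Not attending programmed appointments and voluntary withdrawal will be also contemplated as withdrawals". Reasons for withdrawal are to be recorded, and people who are lost are not replaced. The section does not say whether someone withdrawn by any of these routes is still measured at 6 months.

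The criteria referred to are in section 7.2 and Table 3. Lipid-lowering treatment excludes an index subject. For other family members the same list applies, "except that those following lipid-lowering treatment were included".

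Section 6.2 uses the same event for another purpose: "Adherence to the protocol will be defined as attendance at scheduled visits". Section 6.3 says of the analysis sets: "Both intention-to-treat and per protocol analyses will be performed". Section 8.1.1 makes change in cholesterol the primary outcome.

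Section 8.3 deals with missing values: "Multiple imputations will be used to account for subjects with baseline results but missing results at the end of the trial". It uses 50 imputations, run separately by arm. On the mechanism it says: "When no reason was determined, these data will be deemed missing at random". The sensitivity analysis re-analyses the primary outcome on available cases.

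**The concern.** An intention-to-treat analysis is strongest when the final outcome is measured on everyone randomised, whatever happened to them in between. Section 7.4 works against that. A missed visit or a newly met exclusion criterion becomes an exit from the trial, although the person may be willing and able to give a 6-month blood sample.

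Lipid-lowering treatment is the clearest case. Cholesterol is measured at 3 months (Table 2), and family doctors at the health centre are collaborating researchers (section 5.2). An index subject with high cholesterol could plausibly start treatment during the trial and so become a directed withdrawal before the endpoint. The loss would then be linked to the outcome itself. A relative in the same position is retained and measured.

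At stake is the credibility of the primary comparison. No later analysis plan can recover samples that were never taken.

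**Working it through.** **1. The sections side by side.**
- Sections 6.2 and 7.4: attendance defines adherence, and non-attendance defines withdrawal. One event is therefore both a deviation to tabulate and an exit. The people with observed outcomes and the people who count as adherent largely coincide, so the observed data behind the intention-to-treat and per protocol analyses are nearly the same.
- Sections 7.2 and 7.4: starting lipid-lowering treatment withdraws an index subject but not a relative. If follow-up ends at withdrawal, one analysis mixes imputed values for the first with measured, on-treatment values for the second.
- Sections 7.4 and 8.3: reasons for withdrawal are recorded, but missing at random is declared only where no reason was found. Withdrawals made by rule have a known reason, and no missingness assumption is stated for them.
- Sections 6.3 and 8.3: withdrawn people with baseline results stay in the analysis by imputation. They are not dropped.

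**2. The plan's own power figure (section 5.5).** Inputs: difference 10 mg/dl, SD 36, intraclass correlation 0.25, families of 2 to 4, "a 90% retention rate", alpha 0.05 (taken as two-sided, since section 4.2.2 is non-directional), 250 families at 1:1, so 125 per arm. Taking the 10% loss as whole families leaves 125 × 0.9 = 112.5 per arm. Effective n per arm = 112.5 × m / (1 + (m − 1) × 0.25); power = Φ(10 / (36 × √(2/n)) − 1.96).

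| Mean family size m | Effective n per arm | Power |
|---|---|---|
| 2 | 180.0 | 75.0% |
| 2.5 | 204.5 | 80.2% |
| 3 | 225.0 | 83.8% |
| 4 | 257.1 | 88.3% |

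The claim of more than 80% reproduces from a mean family size of about 2.5 upward.

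**3. Can arm-dependent loss be counted?** Table 1 has intervention entries at weeks 1, 4, 7, 10, 13, 16, 19 and 22, where the control cells are empty. Both arms have entries at 3 and 6 months. If every entry were a programmed appointment, the count would be 10 against 2. If only the assessments in Table 2 qualify, it is 2 against 2. Assume further that attendance is independent across contacts with probability p, and that a single miss is a withdrawal. The share withdrawn is then 1 − p^k:

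| p (assumed) | k = 10 | k = 2 |
|---|---|---|
| 0.95 | 40.1% | 9.8% |
| 0.98 | 18.3% | 4.0% |

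The result runs from a large imbalance to none, depending on a definition that the protocol does not give.

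**4. What outcome-related loss could do.** This is an illustration with inputs not in the documents: baseline correlation 0.7, no clustering, the highest 6-month values lost, and available cases analysed with baseline adjustment. SD 36 and a true difference of −10 mg/dl come from section 5.5.

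| Lost, control / intervention | Estimate (mg/dl) |
|---|---|
| 5% / 5% | −10.0 |
| 2% / 0% | −9.05 |
| 5% / 2% | −8.8 |
| 10% / 5% | −8.2 |

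This is a severe form of loss. With 2 to 4 members per family, index subjects are 1/2 to 1/4 of participants, so a 5% overall loss through drug starts alone needs 10% (0.05 / 0.5) to 20% (0.05 / 0.25) of index subjects to start treatment.

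**The case against.** The strongest reply is that section 7.4 says who counts as withdrawn and does not remove anyone from an analysis set. Section 6.3 promises intention-to-treat, and section 8.3 imputes missing final results for people with baseline data, by arm, with variables that inform missingness. Cholesterol at 3 months is available, so loss driven by that observed value can be handled under missing at random. The exact definition of the analysis set may properly sit in a statistical analysis plan. All of this stands, and it is why a reader who infers a flat contradiction of intention-to-treat goes too far.

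A reader might also infer that the protocol forbids measurement after withdrawal. It is silent; the defect is that a stated withdrawal rule comes with no provision for further outcome collection.

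A third tempting reading is that loss must be heavier in the intervention arm. The documents do not establish this. The entries in Table 1 cannot be read. The three-week spacing matches the food deliveries, and no threshold for missed appointments is given. Drug starts could be commoner in controls if the diet works. Losing high-cholesterol controls would pull the estimate towards zero, while losing poor attenders from the intervention arm could exaggerate it.

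Nor do the documents show that the 90% retention assumption or the power figure fails.

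The reply does not remove two things. Imputation is inferior to measuring a value that could be had. And the available-case analysis is exposed to the same outcome-related loss, so agreement between the two analyses would not be reassuring.

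**Conclusion.** The point holds as a weakness in the data-collection rule. Section 7.4 merges stopping the intervention with leaving follow-up, makes attendance serve as both adherence and retention, and, for index subjects, ties withdrawal to an event linked to cholesterol. This undermines the intention-to-treat analysis without contradicting it.

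The net size and direction of any bias are unknown, as is any effect on retention. The figures of −8.8 and −8.2 mg/dl show what could happen under assumed loss of the highest values without imputation; they are not forecasts. The attendance percentages rest on independence, a one-miss threshold and an unconfirmed count of appointments. Differential loss by arm is plausible but not shown. The point merits correction in the protocol because the remedy depends on samples being taken.

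**What to change.** Reconcile sections 6.2, 6.3, 7.4 and 8.3 as follows:

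- Separate stopping the intervention from ending outcome collection. Whether the intervention continues is left to the investigators and is not changed here.
- Record a missed appointment, or an exclusion criterion that arises after randomisation, as a protocol deviation.
- Keep everyone randomised in the intention-to-treat set and invite them to the 3- and 6-month assessments already scheduled.
- Let only withdrawal of consent or death end outcome collection.
- In section 8.3, state the missingness assumption for data lost for a known reason, and add a sensitivity analysis for the primary outcome that allows for outcome-related loss.

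The cost is protocol wording, a few more measurements at visits that take place anyway, and one further analysis.

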#### 7.5 BASELINE PATIENT CHARACTERISTICS

Baseline characteristics will be described at (1) the family level, i.e., the number of subjects per family, and at (2) the individual level, i.e., age, gender, birthplace, marital status, educational level, employment status, quality of life, physical activity, tobacco and alcohol consumption, personal and family medical history (heart disease, diabetes, high blood pressure, cancer, hypercholesterolemia, age at menarche and menopause) and medication (lipid-lowering and blood pressure-lowering drugs). Health-related quality of life will be assessed using the Spanish v.2.0 of the Short Form 12 Health Survey (SF-12) questionnaire. Answers will be interpreted using reference values for Spanish populations.

Adult physical activity will be assessed using the International Physical Activity Questionnaire (short format) from which the metabolic equivalents and hours per week spent in vigorous and moderate activities, and in walking, as described by Craig et al., will be calculated. This classifies subjects as 'inactive', 'minimally active', and 'HEPA active' (health enhancing physical activity; a high activity category).

273 For subjects under 18 years of age, the enKid rapid questionnaire (the Krece Plus Short  
274 Physical Activity Test)  will be used.

## 275 8 ANALYSIS

---

276  
277 All outcomes will be presented using descriptive statistics - normally distributed data by the  
278 mean and standard deviation, and skewed distributions by the median and interquartile  
279 range. Binary and categorical variables will presented using numbers and percentages.

280 The subsections below describe additional analyses.

### 281 8.1 OUTCOME DEFINITIONS

#### 282 8.1.1 Primary outcome

283 The effects of the intervention on the change in cholesterol levels will be studied via mixed  
284 effects models, with 'family' as a random effect, adjusted for age, gender and cholesterol  
285 level at baseline. The differences in the change in lipid profile will be also examined.

286 Results will be expressed as mean differences (95% CI).

#### 287 8.1.2 Secondary outcomes

288 Mixed effects models will be also used to assess the effect of the intervention on  
289 anthropometric variables, glucose metabolism and inflammatory markers. In these models,  
290 different techniques (e.g., logarithmic transformation) will be used when the distribution of  
291 the dependent variable was non-Gaussian.

#### 292 8.1.3 Specific measurement and units

293 Laboratory results will be reported in conventional units. Anthropometric variables will be  
294 recorded in meters and kilograms.

#### 295 8.1.4 Calculations or transformations used to derive outcomes

296 The body mass index will be defined as a person's weight in kilograms divided by the square  
297 of the person's height in meters (kg/m^2). WHO reference information will be used to  
298 classify and interpret data for adults and children. 

Percentage body fat will be calculated from the skinfold thickness. There are two equations that allow this transformation, that of Siri (the one chosen) and that of Brozek. The homeostasis model assessment-estimated insulin resistance (HOMA-IR) index, developed by Matthews et al. will be used to estimate insulin resistance. This is calculated by multiplying fasting plasma insulin in  $\mu\text{IU/mL}$  (or  $\text{mIU/L}$ ) by fasting plasma glucose in  $\text{mg/dL}$ , then dividing by the constant 405.

## 8.2 DATA VALIDITY AND OUTLIERS

The biomarker results from the laboratory will be automatically downloaded to a database using a computer application. The questionnaires will be filled out by the families in the presence of the nutritionists, who will verify the accuracy of the responses. These data will be independently entered into a database by two operators, and the entries will be compared to detect possible errors. Finally, two researchers will review the database for possible outliers and missing values. In addition, the electronic clinical record of one in every four randomly selected subjects will be reviewed for family history, clinical data, therapeutic prescriptions, and chronic diseases.

### 8.2.1 Normality

All distributions will be checked for normality. Different treatments will be applied if the distributions were non-Gaussian, e.g., logarithmic transformation, GAMLES models, and others.

### 8.2.2 Identifying outliers

Box plots, graphs of the residuals against the fitted values, and the Bacon algorithm, will be used to identify outliers.

## 8.3 MISSING DATA

Missing data will be identified and the reason for their absence investigated. When no reason was determined, these data will be deemed missing at random.

The imputation model will include all the variables, including the dependent variables as well as any other variable that might provide information on the probability of missing data, or about the true values for missing data.

To treat the original data and the multiple imputation data, workflows recommended by StataCorps will be followed.

Multiple imputations will be used to account for subjects with baseline results but missing results at the end of the trial, as well for subjects for whom some data could be not available (biomarkers, anthropometric measurements, surveys, questionnaires, etc.).

Fifty imputations will be performed and the results combined using Rubin's Rules. Imputation will be performed separately for the intervention and control arms.

The distribution of imputed variables will be compared to that of the observed and the complete (i.e., observed and imputed) data.

A sensitivity analysis will be performed to assess the robustness of the results obtained. This involved re-analyzing the primary outcome using techniques not based on multiple imputation (available cases).

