### 5.4 RANDOMIZATION

The participating families will be randomly assigned to either the control or intervention arm (1:1) by a person not associated with the study group, using computer-generated random numbers. This was performed after informed consent was signed.

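### The imputation in section 8.3 is specified by arm and by variables but does not carry the family effect used in the primary analysis

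*Protocol*

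**What the plan says.** On imputation (protocol, section 8.3):

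- Content of the model: "The imputation model will include all the variables, including the dependent variables as well as any other variable" that might inform the chance of a value being missing or its true value.
- Structure: "Imputation will be performed separately for the intervention and control arms".
- Number and pooling: "Fifty imputations will be performed and the results combined using Rubin's Rules".
- Procedure: "workflows recommended by StataCorps", cited to a software manual and not described further.
- Scope: participants with a baseline but no end-of-trial result, and gaps in biomarkers, anthropometry and questionnaires.
- Check: a re-analysis of the primary outcome on available cases, labelled a sensitivity analysis.

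On the family level, elsewhere in the protocol:

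- Families are the randomised unit, 1:1 (section 5.4).
- The change in cholesterol is analysed with mixed "effects models, with 'family' as a random effect, adjusted for age, gender and cholesterol" at baseline (section 8.1.1). Secondary outcomes also use mixed models (section 8.1.2).
- "Further assumptions included an intraclass correlation coefficient of 0.25", with families of 2-4 members and 90% retention (section 5.5).

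Section 8.3 does not mention the family, either to include it or to leave it out.

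**The concern.** An imputation model should carry at least the structure of the analysis model. Here the analysis separates between-family from within-family variation, and the arm effect is a between-family contrast because families are randomised. If a missing value is drawn with no family term, the only resemblance it has to relatives is what passes through covariates such as baseline cholesterol. The completed data then show less clustering than the real data. The mixed model fitted to them estimates a smaller family variance, and the variance between imputations does not make up the difference. Rubin's rules then return a confidence interval for the arm effect that is somewhat too narrow. More imputations would not cure this.

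The stake is the width of the main interval and, to the same small degree, the type I error. Section 8.3 makes the imputed analysis the main one and the available-case analysis the check. For the secondary outcomes no such check is planned.

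**Working it through.** **Inputs from the protocol (5.4, 5.5, 8.1.1, 8.3).** 250 families, 1:1; 2-4 members; ICC 0.25; SD 36 mg/dl; difference 10 mg/dl; retention 90%; alpha 0.05 (taken as two-sided); 50 imputations by arm with Rubin's rules; family random effect with baseline adjustment.

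**Assumptions.** Baseline to follow-up correlation 0.7 (a small pilot run with correlation 0 gave the same SE ratios). Values missing completely at random, either single persons or whole families. Loss of 10% (the plan's figure) and 20% (a range beyond it).

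**Step 1: reproduce the plan's power.** With m members per family, the design effect is DE = 1 + (m - 1) x 0.25, the effective n per arm is 125 x m x 0.9 / DE, and power is Phi(10 / (36 x sqrt(2/n)) - 1.96).

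- m = 2: n = 225/1.25 = 180, power 75.0%.
- m = 3: n = 337.5/1.5 = 225, power 83.8%.
- m = 4: n = 450/1.75 = 257, power 88.3%.

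The stated power above 80% is reproduced at the mid-range family size, so these inputs are a fair basis for what follows.

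**Step 2: expected dilution, by hand.** Without a family term, the residual of each imputed value is drawn independently. A pair of relatives then contributes residual covariance only if both are observed, so residual ICC is roughly 0.25 x P(both observed).

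- 10% loss: persons 0.25 x 0.9 x 0.9 = 0.2025; whole families 0.25 x 0.9 = 0.225.
- 20% loss: persons 0.25 x 0.8 x 0.8 = 0.16; whole families 0.25 x 0.8 = 0.20.

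**Step 3: simulation of the arm effect.** 1,600 trials per scenario with no arm effect, families of 2-4, 50 imputations by arm, Rubin's rules, and a REML random-intercept model adjusted for baseline. SE/SD is the mean reported SE over the true SD of the estimate; rejection is at |estimate/SE| > 1.96.

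| Loss | Imputation | Mean SE | True SD | SE/SD | Rejection | ICC |
|---|---|---|---|---|---|---|
| 10%, persons | no family term | 2.334 | 2.390 | 0.976 | 5.3% | 0.200 |
| 10%, persons | family effect | 2.400 | 2.377 | 1.010 | 4.6% | 0.247 |
| 10%, whole families | no family term | 2.369 | 2.437 | 0.972 | 5.8% | 0.223 |
| 10%, whole families | family effect | 2.452 | 2.440 | 1.005 | 5.1% | 0.248 |
| 20%, persons | no family term | 2.375 | 2.481 | 0.957 | 5.9% | 0.158 |
| 20%, persons | family effect | 2.498 | 2.458 | 1.016 | 4.8% | 0.246 |
| 20%, whole families | no family term | 2.439 | 2.595 | 0.940 | 7.4% | 0.199 |
| 20%, whole families | family effect | 2.612 | 2.581 | 1.012 | 5.1% | 0.249 |

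The simulated ICCs agree with step 2. The available-case mixed model gave SE/SD of 1.00-1.02 in all four scenarios.

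**Step 4: precision.** The Monte Carlo error of a rejection rate is sqrt(0.05 x 0.95 / 1600) = 0.0054, about half a point. That of a single SE/SD ratio is about 1/sqrt(2 x 1600) = 0.018. The methods were run on the same simulated data, so the SEs can also be compared directly. At 10% loss the SE without a family term is 1 - 2.334/2.400 = 2.8% (persons) or 1 - 2.369/2.452 = 3.4% (whole families) below the SE with one.

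**Step 5: second simulation.** 1,500 trials with families fixed at 3 and 12 imputations gave SE/SD of 0.971 and 0.976 at 10% loss (persons, whole families), with rejection 6.07% and 6.00%. At 20% the ratios were 0.961 and 0.939, with rejection 6.1% and 6.7%. Direction and size agree.

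**The case against.** The strongest reply is that section 8.3 never calls its model single-level. It is silent on the level, and its broad inclusion rule could be read to admit family membership, which plainly informs a missing value when the ICC is 0.25. The cited manual is not among the documents, so nothing can be inferred from it. A separate analysis plan may settle the matter. R, listed in section 8.5, leaves room for multilevel imputation.

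Much of this stands, and it limits the point. A reader might infer that the protocol prescribes imputation without the family; the text does not support that. A reader might also infer that imputed relatives become unrelated. They do not: the ICC in the completed data is attenuated, and imputed values still share family-correlated covariates. Nor do the figures establish an inflated type I error at the planned loss. The four rejection rates at 10%, from 5.3% to 6.1%, each lie within two Monte Carlo errors of 5%.

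What does not stand is treating this as mere detail left for later. Section 8.3 fixes the predictors, the number of imputations, the pooling and one structural element, the arm. A programmer following it would stratify by arm and find no instruction to carry the family.

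The available-case re-analysis is a genuine safeguard for the primary outcome if it uses the 8.1.1 model, but section 8.3 does not name the model, and the check does not extend to the secondary outcomes.

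**Conclusion.** The point holds as a conditional one. The imputation described in section 8.3 does not carry the family effect that sections 8.1.1 and 5.5 rely on. Run as described without a family level, it dilutes the residual ICC from 0.25 to about 0.20-0.22 at the planned 10% loss and makes the pooled SE about 2-3% too small, with type I error about 5-6%. At 20% loss, which the protocol does not anticipate, the SE is about 4-6% too small and type I error about 6-7%. Loss of whole families at that rate gave the largest shortfall; it is plausible here because families are invited to baseline together (7.3) and missed appointments count as withdrawal (7.4).

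The figures rest on missingness completely at random, an ICC of 0.25 and the assumed baseline correlation of 0.7. They were computed for cholesterol; the protocol gives no ICC for the secondary outcomes, so the size there is unknown. This is a small, cheaply corrected mismatch and does not by itself undermine the trial.

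**What to change.** In section 8.3, state that imputation is carried out separately by arm with a multilevel model containing a random intercept for family, for the primary and the secondary outcomes, keeping the 50 imputations and Rubin's rules. This can be done in R, already listed in section 8.5. In the same place, state that the available-case re-analysis uses the mixed model of section 8.1.1, so that its protection of the primary outcome is explicit.

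The cost is a sentence or two, some programming, and an interval about 3% wider at the planned loss (2.400/2.334 = 1.028 for person-level loss, 2.452/2.369 = 1.035 for whole-family loss). No further data collection is needed. In the simulations, imputation with a family effect restored SE/SD to 1.01-1.02 and type I error to 4.6-5.1%.
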